#### *Infectious Disease Testing*

Submit the culture medium at the time of liver-derived lymphocyte isolation for aerobic culture test, anaerobic culture test, and endotoxin test. Submit 2 ml of cell culture medium to culture test again 12 hours before administration on the second day of culture. On the day of administration, dispense 2 ml from the cell culture supernatant to the culture test, and confirm the presence of infection by Gram staining in the culture laboratory, and make a judgment based on the results of the infectious disease test submitted during the culture process. A mycoplasma negative test, endotoxin test, and culture test will be submitted from the culture supernatant on the day of shipment, but will not be included in the judgment of shipment.

### 6.3 Container, packaging and storage conditions

Label the container containing the specified cell processing product with a label indication that can be identified by the subject, and store it at room temperature until the shipping decision based on the results of the test inspection is completed.

After the shipping decision is made, the container containing the specified cell processed product is packaged and shipped.

### 6.4 Delivery and transport

The container containing the specified cell products with labels attached is packaged, removed from the cell culture and processing facility, and transported or prepared for transport. The person in charge of the transport transports the specified cell products in the donor transport container to the site of the transplantation surgery. After arriving at the transplantation site, the person in charge of transportation hands over the specified cell products to the person in charge.

### 6.5 Management and storage

Upon arrival at the transplantation site, the physician in charge confirms and receives the number used to identify the subject, the number on the label of the specified cell processing product, and the quality assurance certificate. The specified cell products shall be stored in the designated area of the transplantation site until

use. The expiration date for use shall be within the day of shipment.

## 7 Test Design

### 7.1 Test Design

Single-center, historical data-controlled, open-label study

#### Basis for Design Settings]

This clinical study is a Phase I/II trial of immunostimulatory therapy using activated natural killer (NK) cells derived from liver transplant donors to prevent severe infections after liver transplantation. The safety and efficacy of the administration of liver-derived activated lymphocytes from transplant grafts have been confirmed in a previous Phase I study and in a Phase I study conducted by a collaborative research group in the U.S. in brain-dead liver transplant patients. In this study, based on the results of the previous studies, we set a threshold of 30% incidence of bacteremia in the non-NK group, and conducted an open-label study to ensure that the incidence of bacteremia (percentage) during NK therapy was below the threshold and to collect more safety information during NK therapy.

As for the number of cells to be transplanted, we decided not to set an upper limit because the preclinical studies have shown that the effect depends on the number of cells administered, but there is no difference in the occurrence of adverse events depending on the amount of cells administered, and the number of cells available depends on the donor liver graft, which is difficult to control. In addition, the number of cells available depends on the donor liver graft and is difficult to control.

### 7.2 Target number of enrolled subjects and enrollment period

Target number of enrolled subjects: 37 cases

In a previous study comparing the incidence of bacteremia at one month after living donor liver transplantation in 21 patients in the NK therapy group and 21

[figure not shown]

patients in the matched non-NK therapy group among 114 living donor liver transplants performed from January 2004 to December 2009, the incidence of bacteremia in the non-NK therapy group was 30%, while that in the NK therapy group was 10% (Tashiro et al., Transplantation, 92,p.575, 2011). (Tashiro et al., Transplantation, 92,p.575, 2011). Based on these results, the primary endpoint of this study was the incidence of bacteremia at 1 month after living donor liver transplantation, and the expected incidence rate in the NK therapy group was set at 10%. The number of patients needed to be below the threshold of 30% incidence in the non-NK therapy group at 5% significance level (both sides) and 80% power was calculated to be 34. Considering the dropout cases at the time of enrollment, we set the target number of cases at 37.

Subject enrollment period: From the date of notification of the study to December 31, 2021 (3 years)

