## 15.5 Efficacy analysis

### 15.5.1 Primary endpoints

Incidence of bacteremia within 1 month after living donor liver transplantation  
[Main analysis]

The incidence of bacteremia within 1 month after living donor liver transplantation and its 95% confidence interval will be calculated for FAS. In addition, the following statistical hypothesis test will be performed at a significance level of 5% (two-tailed) by chi-square test using the 30% incidence of bacteremia with non-NK therapy observed in previous studies as a threshold.

The null hypothesis: "The incidence of bacteremia  $p$  in NK therapy is equal to a threshold of 30% ( $p = 0.3$ )."

Counter-hypothesis: "The incidence of bacteremia  $p$  in NK therapy is less than the threshold of 30% ( $p < 0.3$ )"

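### The stated 80% power does not hold at the planned 34 evaluable patients: under the protocol's own chi-square test exact power is 75.0%, and the alternative should be worded to match the two-tailed test

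*Protocol*

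**What the plan says.** Section 7.2 takes bacteremia within one month as the primary endpoint. It uses a "threshold of 30% incidence in the non-NK therapy group" and says that "the expected incidence rate in the NK therapy group was set at 10"%. The number needed "at 5% significance level (both sides) and 80% power was calculated to be 34". It continues: "Considering the dropout cases at the time of enrollment, we set the target number of cases at 37". The overview (section 0) gives the same calculation.

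Section 15.5.1 tests the full analysis set (FAS) "at a significance level of 5% (two-tailed) by chi-square test using the 30% incidence of bacteremia" in non-NK therapy as the threshold. The null hypothesis is p = 0.3. The alternative is that the incidence "in NK therapy is less than the threshold of 30"%, which is one direction only. Section 15.1 repeats that the main analysis is tested at 5%, two-sided. Section 15.2.1 limits the FAS to enrolled patients who were transplanted and given NK cells on postoperative day 3.

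**The concern.** Bacteremia in 34 patients is a whole-number count, so the test can only reject at certain counts and its real power moves in steps as the sample size changes. A smooth approximation can miss this. At 34, which is the protocol's own design point, the step falls the wrong way: one event separates a significant result from a non-significant one, and the favourable count is lower than the formula implies. At stake is the chance that a treatment with the assumed effect fails in the trial's only powered comparison: 25% rather than the 20% stated.

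The second part concerns wording. A two-tailed test allows rejection in either direction, while the written alternative names only one. A reader could then be unsure which count supports a benefit claim.

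**Working it through.** **Inputs.** Threshold p0 = 0.30, expected p1 = 0.10, two-sided 5% (z = 1.96), 80% power (z = 0.8416), 34 evaluable and 37 enrolled, all from section 7.2. The test is a one-sample chi-square against 30%, two-tailed 5%, from section 15.5.1. No continuity correction is assumed, since none is mentioned.

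**1. Reproducing 34.** The usual formula for one proportion is

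n = [(1.96·√(p0(1−p0)) + 0.8416·√(p1(1−p1))) / (p0 − p1)]²

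= [(1.96·√0.21 + 0.8416·√0.09) / 0.20]² = [(0.898 + 0.252) / 0.20]² = 33.1, rounded up to 34.

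The protocol's number is reproduced. At n = 34 the same approximation gives power Φ((0.20·√34 − 0.898)/0.30) = Φ(0.893) = 81.4%.

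**2. The count at which the specified test rejects, n = 34.** The expected count under the null is 34 × 0.30 = 10.2, and its variance is 34 × 0.21 = 7.14.

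- 4 events: (4 − 10.2)²/7.14 = 5.38, two-sided p = 0.020, rejects.
- 5 events: (5 − 10.2)²/7.14 = 3.79, two-sided p = 0.052, does not reject.

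The favourable rejection region is 4 or fewer events.

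**3. Exact power, n = 34.** P(X ≤ 4 | n = 34, p = 0.10) = 0.7504, or 75.0%. The exact lower-tail error is P(X ≤ 4 | n = 34, p = 0.30) = 0.0117. An exact binomial test at one-sided 2.5% has the same cut-off and the same power.

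**4. The other analysis-set sizes that 37 enrolled patients can leave.**

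| FAS | Chi-square cut-off | Two-sided p at cut-off | Exact power at 10% | Exact lower-tail error at 30% |
|---|---|---|---|---|
| 34 | 4 or fewer | 0.020 | 75.0% | 1.2% |
| 35 | 5 or fewer | 0.042 | 86.8% | 2.7% |
| 36 | 5 or fewer | 0.035 | 85.5% | 2.2% |
| 37 | 5 or fewer | 0.029 | 84.0% | 1.7% |

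If more than three patients are lost before dosing, power is again below 80%: 77.0% at 33 and 78.9% at 32. With an exact binomial test at one-sided 2.5%, only the row for 35 changes: the cut-off becomes 4 and power 73.1%, because 5 of 35 has an exact lower-tail error of 2.7%. A continuity-corrected chi-square leaves 34 and 37 as they are, but has cut-off 4 at both 35 and 36, with power 73.1% and 71.1%.

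**5. The two directions of the test.** The two-tailed test also rejects at high counts, from 16 events at 34 and from 17 at 37. Under p = 0.30 the exact probability of such a rejection is 2.7%, 3.6%, 2.2% and 2.9% at n = 34, 35, 36 and 37. Those results lie above 30% and cannot support the written alternative.

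**The case against.** The case for leaving the text alone has four parts.

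- **34 is not a calculation error.** That stands. It follows from a standard formula, and the shortfall comes from the discreteness of the count. What does not follow is that the stated 80% describes the test that will be run.
- **34 is only one possible outcome.** This stands in part. Thirty-seven are enrolled, no dropout rate is stated, and only patients not transplanted or not dosed on day 3 leave the FAS. With 35 to 37 evaluable, chi-square power is above 80%. A reader might infer that the trial as a whole is underpowered, and the figures do not support that. But 34 is the number to which the protocol attaches its 80%.
- **The sidedness is clear.** This largely stands. A reader might infer that the verdict is undetermined at 5 of 34 (two-sided p = 0.052, one-sided 0.026) or 6 of 37 (0.067 and 0.034). However, sections 0, 7.2, 15.1 and 15.5.1 all say two-sided 5% and none mentions a one-sided 5% test. As written, both results fail.
- **The error of a benefit claim is not inflated by the mismatch.** That stands. A two-sided 5% test used in one direction is a one-sided 2.5% test. The upper-tail rejections would point to harm and could not be read as success. The small excess at 35 (2.7%) comes from the chi-square approximation and not from the wording of the alternative.

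**Conclusion.** The point holds in a limited form. At the 34 evaluable patients for which 80% power is claimed, the specified test has 75.0% exact power, a shortfall of 5 percentage points. At 35 to 37 evaluable it has 84.0% to 86.8%. The one-directional alternative beside a two-tailed test is an inconsistency of wording, with no inflation of the benefit error.

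This rests on the protocol's own 30% and 10%, on independent binomial outcomes, and on a chi-square test without continuity correction. The 75.0% at 34 is the same with the correction or with an exact binomial test. The figures at 35 and 36 are less robust: at 35 both alternatives lower the power, and at 36 the correction does.

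**What to change.** In sections 0 and 7.2, keep 34 and 37 but restate the power under the chi-square test: 75% if 34 are evaluable, 84% to 87% if 35 to 37 are.

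In section 15.5.1, state that a benefit is claimed only for an incidence below 30%, at one-sided 2.5%, which is equivalent to the two-sided 5% already written. Say that no continuity correction is used, and give the rule by FAS size: 4 or fewer events at 34, 5 or fewer at 35 to 37.

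An exact binomial test at one-sided 2.5% is a reasonable alternative, since it removes the chi-square's 2.7% lower-tail error at 35. Its price must then be stated: at 35 the cut-off becomes 4 and power falls to 73.1%. Cut-offs and power at 34, 36 and 37 do not change.

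The cost is protocol wording only, with no extra patients. What the sponsor accepts is that stated power is below 80% at 34 evaluable, and also at 35 if the exact test is chosen.

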### 7.3 Possibility of accumulating the target number of enrolled subjects

The total number of liver transplant cases performed at Hiroshima University Hospital from 2008 to 2012 was 97. Since Hiroshima University Hospital performs about 15 liver transplant surgeries every year, if we estimate that the number of patients eligible for this study is about 90% of the above cases, we can expect to obtain about 40 subjects during the 3-year enrollment period, and 37 subjects can be enrolled during the 3-year period even if we take into account the acquisition of consent for participation in the study.

## 7.4 Protocol Treatment Plan

### 7.4.1 Definition of Protocol Treatment

Lymphocyte fractions are extracted from donor graft liver perfusion effluent collected at the time of living partial liver transplantation surgery by the specific gravity centrifugation method. The liver-derived lymphocytes are cultured in complete medium with IL-2 (100 IU/ml) and donor plasma (final concentration 2%) for 3 days. One day prior to administration, anti-CD3 antibody (1 µg/ml) is added to the medium to remove CD3 positive T cells. The cell suspension is collected, centrifuged, and washed with saline, and then the cells are suspended in albumin-containing saline and administered as a single dose to the liver transplant recipient

transvenously on postoperative day 3. Protocol treatment is defined as from donor graft liver perfusion to the completion of donor liver-derived activated NK cell administration.

#### 7.4.2 Method

- 1) Preparation of Activated Natural Killer (NK) Cells from Liver Transplant Donor Livers  
It is shown in the section "Manufacturing Methods."

- 2) Administration of activated natural killer (NK) cells derived from liver transplant donor livers

After culture and confirmation of safety by infectious disease testing, a single dose of cell suspension is administered intravenously over 30 minutes to 1 hour to liver transplant recipients on day 3 after living partial liver transplantation.

#### 7.4.3 combination therapy

Treatment considered necessary before and after living donor liver transplantation surgery should follow the usual postoperative management of living donor liver transplantation performed at Hiroshima University Hospital, and can be performed at any time.

#### 7.4.4 Infectious Disease Treatment

Treatment of infectious diseases is left to the judgment of the physician in charge, based on a comprehensive assessment of the site, extent, and tolerability of treatment in each case.

#### 7.4.5 Rationale for establishing a protocol treatment plan

Since this clinical study is not expected to have any impact on the surgical management of living partial liver transplantation, all procedures other than this postoperative adjuvant immunotherapy will be performed in accordance with the conventional perioperative management.

#### 7.4.6 Duration of study participation of enrolled subjects

The treatment period is from donor graft liver perfusion to the completion of donor liver-derived activated NK cell administration, and the observation period is up to 3 years after living partial liver transplantation surgery.

## 7.5 in-progress total

An interim tally will be made at the end of the observation period of one month after the surgery in the 15th case in which NK cells were administered, and the Effectiveness and Safety Evaluation Committee will consider whether the study should be continued. The Efficacy and Safety Evaluation Committee will determine whether or not to continue the study, based on the achievement of the primary endpoint and from the safety perspective, if the incidence of bacteremia within 1 month after surgery is 6 or more cases (40% or more) out of 15 cases, and if the incidence of adverse events of Stage 3 or higher that cannot be ruled out as causally related to NK cell administration is 2 or more cases. The efficacy and safety evaluation committee will consist of three physicians, excluding the research subcontractor.

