#### ■ Activated NK cell therapy for the prevention of hepatocellular carcinoma recurrence after living donor liver transplantation at Hiroshima University (paper in preparation)

Twenty-four patients with hepatocellular carcinoma (HCC) within the preoperative Milan criteria underwent donor liver-derived activated lymphocyte transfer as adjuvant immunotherapy after liver transplantation. The median age of the patients was 58 years, 17 were males and 7 were females. The median number of activated lymphocytes administered was  $270 (38-820) \times 10^6$  cells/body. 5-year overall survival rate and 5-year relapse-free survival rate were 82.5% and 74.5%, respectively. No GVHD was observed in patients receiving immunotherapy, and no other serious dose-related adverse events were observed. There was no significant difference in the incidence of Grade 3/4 (CTCAE ver. 4) or higher adverse events between the high-dose group ( $> 270 \times 10^6$  cells/body) and the low-dose group ( $\leq 270 \times 10^6$  cells/body). There was no significant difference in the frequency of Grade 3/4 (CTCAE ver.4) or higher adverse events between the immunotherapy group and the non-immunotherapy group. The quantitative antidonor response by CFSE-MLR (lymphocyte mixing test using CFSE dye) did not differ between immunotherapy and non-immunotherapy groups.

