### 10.3 Assessment of adverse events

Adverse events observed during the conduct of clinical research will be evaluated according to the schedule specified in "Observation and Examination Items and Schedule".

The severity of adverse events will be determined based on the NCI-Common Terminology Criteria for Adverse Events (NCI-CTC-AE Ver4.0 Japanese version).

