### 13.2 Criteria and procedures for interruption or discontinuation of the entire clinical study

#### 13.2.1 Criteria for interruption or discontinuation of clinical research as a whole

The principal investigator will consider whether or not to continue the clinical research if any of the following applies

1. When significant information on the quality, safety, or efficacy of NK cell preparations is obtained
2. When it is judged difficult to complete the clinical research due to reasons such as delay in case enrollment or frequent deviation from the protocol.
3. If the safety of the protocol treatment is judged to be problematic based on the evaluation of the Hiroshima University Committee for Regenerative Medicine, etc.
4. If, as a result of evaluation of relevant information obtained from sources other than this clinical study, such as papers and conference presentations, it is

determined that there is a problem with the safety of the protocol treatment, or that the continuation of the clinical study is no longer meaningful.

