### 16.4 Effectiveness and Safety Evaluation Committee

#### 16.4.1 Details of deliberations by the Effectiveness and Safety Evaluation Committee

The Efficacy and Safety Evaluation Committee shall consist of three physicians, excluding the subcontractors, and shall deliberate on the following matters

- Contents of the annual implementation status report
- Confirmation of the efficacy and safety of the NK cells and whether the study should be continued at an interim total to be conducted at the end of the observation period of one month after the 15th surgery in which NK cells were administered.
- Assessment of serious adverse events
- Other matters as deemed necessary by the principal investigator or the Efficacy and Safety Evaluation Committee.

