## 17.2 Deliberations of the Committee for Regenerative Medicine, Hiroshima University

The Hiroshima University Committee for Regenerative Medicine will deliberate on the following matters.

1. Progress check
2. Whether or not to continue the research due to the occurrence of serious adverse events
3. Other matters deemed necessary by the chairperson

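### Section 7.5 joins its two numeric interim thresholds with 'and if', so on a literal reading the related-toxicity threshold has almost no force by itself

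*Protocol*

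**What the plan says.** Protocol section 7.5 places an interim tally one month after surgery in the 15th case given NK cells. Its first sentence sets no numeric condition: "the Effectiveness and Safety Evaluation Committee will consider whether the study should be continued".

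The next sentence has the committee determine continuation on two grounds, the primary endpoint and safety, and states two thresholds. One is bacteremia within a month of surgery in 6 or more of 15 cases. The other, with a minimum count of two, follows directly: "and if the incidence of adverse events of Stage 3 or higher that cannot be ruled out as causally related to NK cell administration". Neither *or* nor *either* appears, and no other section says that one threshold is enough.

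Other sections bear on the point:
- Section 13.2.1, on the principal investigator's criteria for stopping the whole study, marks alternatives plainly: "consider whether or not to continue the clinical research if any of the following applies".
- Section 16.4.1 repeats the interim review without the thresholds, "Confirmation of the efficacy and safety of the NK cells and whether the study should be continued at an interim total", and separately lists "Assessment of serious adverse events".
- Section 17.2 gives the Regenerative Medicine Committee its own remit: "Whether or not to continue the research due to the occurrence of serious adverse events".
- Section 10.3 fixes the severity scale: "The severity of adverse events will be determined based on the NCI-Common Terminology Criteria for Adverse Events". Section 2.2.3 uses the matching label, "Grade 3/4 (CTCAE ver. 4) or higher adverse events", where 7.5 says Stage 3.

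**The concern.** These are the only numeric interim thresholds in the protocol. Joined by *and if*, a count of related severe events would meet the criterion only if bacteremia were also high. That fits poorly with the sentence's own two grounds, because a safety signal would then count only when efficacy also looked poor. The awkward case is the one the design hopes for on efficacy: few bacteremias, but several related severe events.

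With 2 related severe events and 1 bacteremia, for example, the text does not settle whether the pre-specified criterion was met. That would be decided after the data had been seen, which is what a pre-specified threshold is meant to avoid.

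**Working it through.** **Inputs.** From 7.5: 15 cases, bacteremia threshold 6, related severe event threshold 2. From 7.2: expected bacteremia 10%, threshold rate 30%. The protocol gives no rate for related severe events, so I assume a range for it, written *q*.

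**The plan's own figure.** 6/15 = 0.40, which agrees with the 40% in 7.5.

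**Bacteremia threshold alone.** With X ~ Bin(15, p),

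P(X ≥ 6) = 1 − Σ_{k=0..5} C(15,k) p^k (1−p)^(15−k)

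This is 0.0022 at p = 0.10 and 0.2784 at p = 0.30.

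**Safety threshold alone.** With Y ~ Bin(15, q),

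P(Y ≥ 2) = 1 − (1−q)^15 − 15q(1−q)^14

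At q = 0.10 this is 1 − 0.20589 − 0.34315 = 0.4510.

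**Both thresholds: a bound without independence.** A joint event cannot be more likely than its rarer part. At p = 0.10, P(X ≥ 6 and Y ≥ 2) ≤ 0.0022 for every q and every correlation.

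**Both and either, if the two counts are independent.** Both = A × B and either = A + B − A × B, where A and B are the two single-threshold probabilities.

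| Assumed q | Safety alone | Both, p = 10% | Either, p = 10% | Both, p = 30% | Either, p = 30% |
|---|---|---|---|---|---|
| 2% | 0.035 | 0.0001 | 0.038 | 0.0098 | 0.304 |
| 5% | 0.1710 | 0.0004 | 0.1728 | 0.0476 | 0.4017 |
| 10% | 0.4510 | 0.0010 | 0.4522 | 0.1255 | 0.6038 |
| 20% | 0.8329 | 0.0019 | 0.8332 | 0.2319 | 0.8794 |
| 30% | 0.9647 | 0.0022 | 0.9648 | 0.2686 | 0.9746 |

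**If the counts overlap.** Section 10.4.1 lists infections among the anticipated adverse events, so one patient may enter both counts. In the extreme case, every bacteremia is also counted as a related severe event. Then Y ≥ X, so 6 bacteremias already give at least 2 events. The joint probability equals P(X ≥ 6): 0.0022 at 10% and 0.2784 at 30%. The bacteremia threshold then loses nothing. The safety threshold still does: alone it would be met with probability at least P(X ≥ 2) = 0.4510 at 10% bacteremia, against 0.0022 jointly.

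**The case against.** The strongest reply is that two separate triggers were meant. The sentence repeats *if*, which is a normal way to list distinct conditions, and its two named grounds match the two thresholds in order. The document also reads like a rough translation (its recipient schedule is still in Japanese), so a single conjunction is thin evidence of intent. The contrast with 13.2.1 is imperfect, since that is a numbered list addressed to the principal investigator. All of this stands, and it makes separate triggers the likelier intent. It does not settle the text, because no section says that either threshold suffices.

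The second reply is that nothing turns on the clause: the committee considers continuation at the 15th case anyway, and meeting the thresholds stops nothing automatically. This stands too, and it keeps the point small. But the general review carries no numbers. If the thresholds have any function, the text must say when they are met.

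Third, the upper end of the assumed event range has no support in the documents. Section 2.2.3 reports no GVHD and no other serious dose-related events in 24 earlier patients. That is fair for the 83% and 96% figures. The 0.2% ceiling does not depend on the event rate.

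A reader might infer that toxicity could go unreviewed unless bacteremia were also high. The documents do not support that: 7.5 and 16.4.1 hold the review whatever the counts, and 13.2.1, 16.4.1 and 17.2 give other safety routes.

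**Conclusion.** The point holds as a minor fault in the wording of a stated decision rule. Taken literally, 7.5 requires both thresholds before the committee's determination is called for. At the expected 10% bacteremia, that criterion is met in at most 0.2% of trials, so the numeric safety threshold has almost no force. This bound rests only on 15 cases and a 10% bacteremia rate with patients independent of one another; it needs no event rate and no independence between the two counts. The comparison figures for the safety threshold alone (17%, 45%, 83% and 96% at 5%, 10%, 20% and 30%) rest on assumed rates.

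These percentages are chances of meeting the clause, not chances of harm being missed. Nor does the point reach the error rates or the final analysis, as a reader might suppose: the thresholds prompt a committee decision, and the main test in 15.5.1 is unchanged by the edit. Stage for Grade is a clerical slip and would not merit a comment on its own.

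**What to change.** In 7.5, list the two thresholds as numbered criteria and state that meeting either one alone requires the committee's formal decision on continuation. Keep 6 of 15 and 2 cases as they are. In the same edit, replace Stage 3 with Grade 3 (CTCAE v4.0), to agree with 10.3.

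This changes one sentence; sample size, interim timing and analysis stay the same. The downside is that formal decisions are required more often. From the *either* columns of the table, for event rates of 5%, 10%, 20% and 30%, one would be required in 17%, 45%, 83% and 96% of trials at 10% bacteremia, and in 40%, 60%, 88% and 97% at 30% bacteremia. The added burden is modest, since the committee already considers continuation at this interim in every case.
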